## Abstract

**Background:**

The increasing prevalence of cardiometabolic disease (CMD) in combination with an ageing population is a major public health problem. Early detection and management of individuals at risk for CMD is required to prevent future health problems with associated costs. General practice is the optimal health care setting to accomplish this goal. Prevention programs for identification and treatment of patients with an increased risk for CMD in primary care have been proven feasible. However, the effectiveness and cost-effectiveness have yet to be demonstrated. The ‘Personalized Prevention Approach for CardioMetabolic Risk’ (PPA CMR) is such a prevention program. The objective of the INTEGRATE study is to investigate the effectiveness and cost-effectiveness of PPA CMR, as well as to establish determinants for participation and compliance.

**Methods:**

The INTEGRATE study is designed as a stepped-wedge randomized controlled trial with a waiting list control group. In approximately 40 general practices, all enlisted patients without CMD aged 45–70 years, are invited to participate in PPA CMR. After an online risk estimation, patients with a score above risk threshold are invited to the GP for additional measurements, detailed risk profiling and tailored treatment of risk factors through medication and/or lifestyle counseling. At baseline and after twelve months of follow-up lifestyle, health and work status of all participants are established with online questionnaires. Additionally after twelve months, we will determine health care utilization, costs of PPA CMR and compliance. Primary endpoints are the number of newly detected patients with CMD and changes in individual risk factors between the intervention and waiting list control group. Medical data will be extracted from the GPs’ electronic medical records. In order to assess factors related to participation, we will send questionnaires to non-participants and assess characteristics of participating practices. For all participants, additional demographic characteristics will be available through Statistics Netherlands.

**Discussion:**

The INTEGRATE study will provide insight into the effectiveness and cost-effectiveness of PPA CMR as well as determinants for participation and compliance, which represents essential information to guide further large-scale implementation of primary prevention programs for CMD.

**Trial registration number:**

NTR4277, The Netherlands National Trial Register, 26-11-2013.

## Background

The increasing prevalence of cardiometabolic disease (CMD), including cardiovascular disease, diabetes mellitus and chronic kidney disease, in combination with an ageing population is a major public health problem. CMD mainly results from a long lasting exposure to an unhealthy lifestyle. The most important lifestyle related causes of morbidity and mortality are smoking, obesity and physical inactivity [1]. The increasing number of people with an unhealthy lifestyle is expected to lead to a rising prevalence of CMD in the coming decades [2-4]. Therefore, early detection and adequate management of individuals at risk for CMD is urgent in order to prevent future health problems and further increase in health care costs.

Screening for CMD could be more efficient when structurally embedded in primary health care [5,6]. General practitioners (GPs) can play an important role in preventing CMD [7]. General practice is the optimal setting for identifying and treating patients at risk [8]. GPs provide integrated health care, are aware of the psychosocial context and have a longstanding relationship with their patients.

Several prevention programs for CMD in primary care have been developed. These programs aim to identify patients at risk for CMD and to offer lifestyle advice and treatment when indicated [9-13]. The core elements of these programs are evidence-based and the feasibility has been positively evaluated [9-12,14-18]. Different parties have initiated implementation by offering their program to subgroups within the general population. However, the effectiveness and cost-effectiveness of prevention programs for CMD need to be established first to justify broad implementation in primary care [19]. An effective prevention program also requires structured health care, willingness to participate and compliance of patients at risk. So far, little is known about the characteristics of practices, participants and non-participants in prevention programs in primary care [20-22]. Knowledge about determinants for non-participation will support the development of tailored strategies to reach specific subgroups. In the INTEGRATE study we aim to assess the effectiveness of a CMD prevention program coupled to an individualized lifestyle intervention. This entire program will be further referred to as “Personalized Prevention Approach for CardioMetabolic Risk” (PPA CMR). Therefore, the objective of the INTEGRATE study is to investigate the effectiveness and cost-effectiveness of PPA CMR, as well as to asses determinants for successful participation in PPA CMR. In this paper we will describe the design of the study and we will discuss the choices that have been made for the intervention and with regard to outcome measures.

## Methods

### Study design

The INTEGRATE study is a clustered stepped-wedge randomized controlled trial with a waiting list control group. A flowchart of the study and a timeline is shown in Figures 1 and 2, respectively. All participants are offered the intervention (PPA CMR) during the study period. The intervention is implemented over four time periods, in randomly ordered subgroups. The intervention group starts with PPA CMR at onset of the study, the control group starts with PPA CMR one year later. The one year waiting list period is necessary to measure natural changes in lifestyle and to estimate the number of patients with newly detected CMD without exposure to PPA CMR.

**Figure 1 F1:**
[figure not shown]
Flowchart of the study design.

**Figure 2 F2:**
[figure not shown]
**Timeline per practice and overview of measures**. Legend: • = All patients, o = Patients with an increased risk for CMD. Q = questionnaire, P = primary outcome measure, S = secondary outcome measure.

### Study population

The study will be conducted in approximately 40 general practices in the Netherlands, a representative sample of all Dutch general practices with regard to the distribution in rural/urban and solo/group practices. Inclusion and exclusion criteria for practices and patients are shown in Table 1.

**Table 1 T1:** Inclusion and exclusion criteria for practices and participants

	**Inclusion**	**Exclusion**
**General practices**	• Use of common Electronic Medical Record (EMR) system, in which electronic data extraction is possible	• Recently performed screening for patients at risk for cardio-metabolic disease
**Patients**	• Age between 45 and 70 years	• Receiving antihypertensive or lipid-lowering treatment
		• One of the following ICPC-I-codes: K74: Angina pectoris, K75: Acute myocardial infarction, K76: Other chronic ischaemic heart disease, K77: Heart failure, K86: Uncomplicated hypertension, K87: Hypertension with secondary organ damage, K89: Transient cerebral ischemia, K90: Stroke/cerebrovascular accident, K91: Atherosclerosis, K92: Peripheral vascular diseases, T90: Diabetes mellitus, T93: Lipid metabolism disorder

Inclusion criterion for practices:

•The use of an Electronic Medical Record (EMR) system, from which electronic data extraction is possible, covering approximately 90% of all Dutch general practices.

Exclusion criterion for practices:

•Previously performed systematic CMD screening of the entire or a non-random sample of the practice population.

All eligible patients of the included practices (approximately 28.500 patients) receive an invitation letter from their GP to participate in the INTEGRATE study.

Inclusion criterion for patients:

•Age between 45 and 70 years, which is according to the guideline of the Dutch College of GPs [13].

Exclusion criteria for patients:

•Previous diagnosis of CMD according to EMR (see Table 1 for list of International Classification of Primary Care (ICPC-1)-coded diagnoses [23]).

•Receiving antihypertensive and/or lipid-lowering treatment.

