#### Completing the CMD risk profile

At the general practice, the risk profile is completed by additional measurements: serum cholesterol level, fasting glucose level and blood pressure. During a second visit the final risk profile is calculated based on the SCORE risk estimation [27].

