### Endpoints and measurements

The endpoints of the INTEGRATE study are shown in Table 2. An overview of all measurements is shown in Figure 2.

**Table 2 T2:** Primary and secondary endpoints

**Primary endpoints**	**Secondary endpoints**
1. The number of newly detected patients with a CMD in one year follow-up	1. Difference in primary outcome 5 after implementation of different response-enhancing strategies
2. Change in individual risk factors (smoking, physical inactivity, obesity, unhealthy diet, blood pressure and cholesterol levels) for CMD between baseline and one year follow-up	2. Change in willingness to change lifestyle between baseline and one year follow-up
3. The expected number of newly detected patients with CMD and mortality after 5, 10,20 years and lifetime	3. Change in health status between baseline and one year follow up
4. Costs-effectiveness of PPA CMR	
5. Non-participation and compliance in different stages of PPA CMR	

For our secondary endpoints we will use the information provided for our primary endpoints.

1. *Newly detected patients with CMD at baseline and one year follow-up*

The number of newly detected patients with pre-existing CMD will be established after the second consultation and after one year follow-up, based on ICPC-1-coded diagnoses (see Table 1) in the EMRs.

2. *Change in individual risk factors for CMD between baseline and one year follow-up*

For patients with an increased risk for CMD, risk and lifestyle profiles will be established at the start of PPA CMR and after twelve months of follow-up. Risk profiles consist of the completed risk profile including the additional measurements done by the GP or with the self-management toolbox. The questions of the online risk estimation and lifestyle assessment are repeated after six months as well (see Figure 2).

For patients with a low risk for CMD we will establish risk and lifestyle profiles at the start of PPA CMR and after twelve months of follow-up. These risk profiles do not contain the additional measurements.

3. *Expected newly detected patients with CMD and mortality after 5, 10, 20 years and lifetime*

We will use the RIVM-Chronic Disease Model (RIVM-CDM) [28,29] to extrapolate the number of possible prevented CMD due to PPA CMR with a time horizon of 5, 10 and 20 years. The calculations are based on changes in risk profile during one year of treatment.

4. *Costs-effectiveness of PPA CMR*

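### Known diabetes is excluded by code only, so a treated but uncoded patient can count as newly detected; separately, Table 2 omits the glucose that the endpoint 2 text includes

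*Protocol article*

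**What the plan says.** **Entry.** Diabetes is one of the target diseases: the Background defines cardiometabolic disease (CMD) as "including cardiovascular disease, diabetes mellitus and chronic kidney disease". Under Study population, patients with a listed ICPC code are excluded, and the list ends with "T90: Diabetes mellitus, T93: Lipid metabolism disorder". A second patient criterion works through treatment. Table 1 words it as "Receiving antihypertensive or lipid-lowering treatment" and the text list as "Receiving antihypertensive and/or lipid-lowering treatment". Neither names glucose-lowering treatment.

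**Endpoint 1.** Newly detected CMD is established after the second consultation and at one year, "based on ICPC-1-coded diagnoses (see Table 1) in the EMRs". The code list used to exclude patients is thus also the list used to count detections.

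**Endpoint 2.** Table 2 lists the individual risk factors as "smoking, physical inactivity, obesity, unhealthy diet, blood pressure and cholesterol levels". The text for endpoint 2, for patients at increased risk, says: "Risk profiles consist of the completed risk profile including the additional measurements done by the GP". Those measurements are defined under Completing the CMD risk profile as "serum cholesterol level, fasting glucose level and blood pressure".

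**The concern.** A count of new detections is sound only if disease that was already known has been removed at entry. For hypertension and lipid disorder there are two safeguards: if the code is missing, the drug criterion still catches the treated patient. For diabetes there is one. A patient already treated for diabetes whose record lacks T90 passes the filter, and a later T90 code is then indistinguishable from a true detection. At stake is the specificity of the first primary endpoint and, if coding is prompted more in one arm than in the other, a small error in the between-arm comparison.

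The second issue is one of definition. Three biomedical measurements enter the risk profile on which endpoint 2 rests, but Table 2 names only two of them. A reader cannot tell whether change in fasting glucose is an outcome of this trial.

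**Working it through.** **1. Criteria side by side (Study population; Endpoints and measurements)**

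| Condition | Excluded by code | Excluded by drug treatment | New code counts in endpoint 1 |
|---|---|---|---|
| Hypertension | K86, K87 | yes | yes |
| Lipid disorder | T93 | yes | yes |
| Diabetes | T90 | no | yes |

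The patient in question must meet three conditions at entry: on glucose-lowering treatment, no T90 code, and on neither antihypertensive nor lipid-lowering treatment. Nothing in the endpoint 1 text removes such a patient from the count later.

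**2. Inputs for size.** The plan gives no figure for this point, so there is none to reproduce. From the Sample size calculation: 21 intervention patients per practice at twelve months and about 40 practices (721/21 = 34.3; 34.3 × 1.15 = 39.5). This gives N = 21 × 40 = 840. The 721 itself reproduces exactly (25% versus 20%, two-sided 0.05, 80% power, 1:4, with continuity correction) and does not depend on this point.

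Assumptions, not in the documents: u, the share of entrants who are treated but uncoded, is 0.1% to 0.5%; c1 and c0 are the proportions of them who receive T90 within the year in the intervention and control arms.

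**3. False detections in the intervention arm** = N × u × c1.
- Upper limit, c1 = 1: 840 × 0.001 = 0.84 to 840 × 0.005 = 4.2, or about 1 to 4 patients.
- With c1 = 0.5: 0.42 to 2.1 patients.

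**4. Share of all detections.** Endpoint 1 counts any of twelve codes. If total yield were 10% (a further assumption), 840 × 0.10 = 84 detections, and the upper-limit share is 0.84/84 = 1% to 4.2/84 = 5%.

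**5. Between-arm excess per 1,000** = 1000 × u × (c1 − c0).

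| c1, c0 | u = 0.1% | u = 0.5% |
|---|---|---|
| 1, 0 (worst case) | 1.0 | 5.0 |
| 0.5, 0.1 | 0.4 | 2.0 |
| equal | 0 | 0 |

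With equal coding both counts are inflated, but the difference is not.

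**6. Endpoint 2.** Table 2 has six risk factors, including blood pressure and cholesterol but not glucose. The endpoint 2 text takes in the additional measurements, which are cholesterol, fasting glucose and blood pressure, at the start and at twelve months. Table and text do not match, and no reason is given.

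**7. What controls have measured.** The Control group section describes an online questionnaire at baseline and no blood test. The later section on the waiting list control group speaks of risk profiles at baseline and one year later without saying that they include the additional measurements. A baseline control value is therefore not clearly scheduled for glucose, nor for cholesterol.

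**The case against.** The strongest reply on entry is that the asymmetry may be intended. The programme itself can lead to drug treatment according to risk profile, so people already on preventive blood-pressure or lipid drugs might be excluded for that reason, with or without a diagnosis. A reader might infer from the drug criterion that the authors distrusted the codes; the article does not say so. This reply stands as to motive. It does not close the gap, because the rule as written still admits the patient described and the endpoint still counts that patient.

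On size, the objection largely stands. No rate is documented. To be coded through the programme, a patient must respond, score above the threshold, attend and have T90 entered, so the upper limit in the working is generous. A reader might set the 0.84 to 4.2 false cases against diabetes alone: with an assumed true yield of 1% to 2% (8.4 to 16.8 cases), the overstatement runs from 0.84/16.8 = 5% to 4.2/8.4 = 50%. The 50% pairs the highest assumed false rate with the lowest assumed true rate, and endpoint 1 is not a diabetes count.

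On direction, a reader might infer that the gap favours the programme. Above-threshold intervention patients have fasting glucose measured and the profile reviewed at a second visit, while controls stay in usual care, so this is plausible. But usual care includes diagnostics for CMD when indicated, a treated patient is already under care, and randomisation within practices balances such patients at entry. Unequal coding is not shown.

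On the outcome, a reader might infer from Table 2 that glucose belongs to no endpoint and that the trial can say nothing about it. The documents do not support that. The endpoint 2 text includes it, diabetes reaches endpoint 1 through T90, and Figure 2, which marks measures as primary or secondary, was not available to check.

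**Conclusion.** The point holds in a limited form. The entry rule protects against counting known hypertension and lipid disorder as new when the code is missing, but gives no such protection for diabetes, and endpoint 1 as defined would count the resulting T90 codes. The effect is probably small: at most about 1 to 4 of 840 intervention patients, if 0.1% to 0.5% of entrants are treated but uncoded and every one of them is later coded. That is a small share of all detections. It distorts the comparison between arms only so far as the programme prompts more coding than usual care. Misclassification is something the criteria allow, not something the documents show to occur.

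The glucose outcome is a mismatch between Table 2 and the endpoint 2 text, not an absent measurement. It needs no assumed rate and should be reconciled. The sample size is unaffected by either part.

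**What to change.** **Entry and endpoint 1.** In Table 1 and in the text list, extend the treatment criterion to antihypertensive, lipid-lowering or glucose-lowering treatment, and apply it in the same extraction from the electronic records before randomisation. If the lists are already drawn, use the baseline records to flag patients on glucose-lowering treatment without T90, identically in both arms, and state that a later T90 code in a flagged patient is not a new detection.

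**Endpoint 2.** Reconcile Table 2 with the endpoint text by naming fasting glucose as a secondary outcome, so that the primary set does not grow. Analyse it with the planned linear multilevel model, in the same patients and at the same times as cholesterol. State at which times each arm has blood measurements, and limit any between-arm comparison to times when both are measured; do not rely on a control baseline value unless one is in fact scheduled.

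**Cost.** One drug class added to an existing query, a very small loss of eligible patients, and one more secondary comparison.

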### Randomization

Eligible patients are randomized within each general practice into four time groups: two intervention groups and two waiting list control groups. We will use the statistical software program Stata version 12 for the randomization. Every four months a new group starts with the intervention, starting with the two intervention groups. After twelve months the two waiting list control groups will sequentially start with PPA CMR.

### Intervention

The intervention program “Personalized Prevention Approach for Cardiometabolic risk” (PPA CMR) is the combination of a screening tool for CMD as used in the professional guideline ‘Preventive Consultation’ (PC) of the Dutch College of General Practice [13] and a tailored lifestyle intervention. PC is a Dutch prevention program for CMD and has been developed for integration in primary care (in Dutch: ‘PreventieConsult Cardiometabool risico’). In a pilot study in 2009 the PC has been tested with regard to its feasibility and was positively evaluated [8,15,17,24].

The intervention program of the INTEGRATE study consists of several steps:

1. Invitation of patients to assess their CMD risk.

2. First step of screening: the online risk estimation and lifestyle assessment.

3. Second step of screening: completing the CMD risk profile with additional measurements.

4. Treatment of patients with an increased risk for CMD with tailored lifestyle advise and/or medication.

#### Invitation of patients

All eligible patients receive an invitation from their GP to participate in PPA CMR by completing an online risk estimation and optionally an online lifestyle assessment. To enhance participation rates, the accompanying information letter will summarize the details of the study in different languages. In case of non-response, a reminder letter is sent after two weeks. Enclosed with the reminder letter is a paper version of the risk estimation.

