#### The risk estimation and lifestyle assessment

The risk estimation is based on the widely accepted FINDRISK score and is specified for predicting CMD in the Dutch population [25,26]. This seven item-questionnaire can be completed by self-report and assesses cardiometabolic risk factors including age, gender, body mass index, waist circumference, current family history of cardiovascular disease and/or diabetes [13,26]. The lifestyle assessment consists of questions involving smoking, physical activity, dietary patterns and willingness to change lifestyle [9,12].

The threshold in the risk estimation that will be used is an absolute risk for developing CMD in the next seven years of ≥ 23% for men and ≥ 19% for women [26]. Patients with scores below the threshold are at low risk and receive online tailored lifestyle advice based on the reported risk factors and the information provided in the lifestyle assessment. All patients with scores above the threshold are advised to complete their final risk profile with additional measurements, by making an appointment at their general practice.

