### Control group

Patients allocated to the waiting list control group receive an invitation from their GP - at the same moment the first intervention group is invited- to participate in a health study by completing an online questionnaire including the questions of the risk estimation and lifestyle assessment. However, these patients neither receive a risk score, nor a specific lifestyle advice. These patients will start with a one year waiting period, to be used as control comparison. After a year they are invited to participate in PPA CMR, starting with completing the risk estimation and lifestyle assessment online. Hence, the waiting list control group is offered the identical route as the intervention group. Patients in the waiting list control group receive normal standardized care during the waiting period, including lifestyle advice or diagnostics and treatment for CMD when indicated.

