#### Sample size calculation

Calculation of the sample size is based on the reduction of smokers in the intervention group after one year follow-up, one of the primary outcome measures. The smoking prevalence in the Netherlands is 25% [35]. We expect a reduction in smoking prevalence from 25% to 20% after one year treatment and a stable number of smokers in the waiting list control group. In order to achieve this reduction, 721 patients are needed in the intervention group. This calculation is based on an alpha of 0.05 (two-sided), a power of beta = 0.80 and a ratio intervention group versus control group of 1:4). The 1:4 ratio represents a fair comparison between the intervention and the large control group. Based on the pilot implementation study of the PC, we expect approximately 21 patients per practice in the intervention group after twelve months follow -up [14,15]. A low response rate has been taken into account with this estimate. This would result in the inclusion of 721/21 = 34 general practices. However, in this study patients are clustered within general practices and an oversampling of 15% is needed to correct for this clustering in multi-level analyses. Therefore, we need approximately 40 general practices. The number of participants and practices will result in sufficient power to establish statistically significant differences between other subgroups.

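### The questions on physical activity, diet and possibly smoking are optional at baseline for PPA CMR invitees but built into the control questionnaire, so part of primary endpoint 2 may be collected differently by arm

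*Protocol article*

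**What the plan says.** All references are to the protocol article.

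- **Invitation of patients.** PPA CMR invitees take part "by completing an online risk estimation and optionally an online lifestyle assessment". For those who do not respond, "Enclosed with the reminder letter is a paper version of the risk estimation". No paper lifestyle assessment is mentioned.
- **The risk estimation and lifestyle assessment.** "The lifestyle assessment consists of questions involving smoking, physical activity, dietary patterns and willingness to change lifestyle". The risk estimation is described as having seven items and "assesses cardiometabolic risk factors including age, gender, body mass index, waist circumference, current family history of cardiovascular disease and/or diabetes". Smoking, activity and diet are not named there.
- **Control group.** Waiting-list patients complete "an online questionnaire including the questions of the risk estimation and lifestyle assessment". No part is called optional. They receive neither a score nor specific advice.
- **Endpoints and measurements, Table 2.** Primary endpoint 2 is "Change in individual risk factors (smoking, physical inactivity, obesity, unhealthy diet, blood pressure and cholesterol levels"), from baseline to one year.
- **Sample size calculation.** "Calculation of the sample size is based on the reduction of smokers in the intervention group after one year follow-up".
- **Statements that point the other way.** The Abstract (Methods) has lifestyle recorded for every participant at baseline and twelve months. Endpoints and measurements has lifestyle profiles set up at the start for both high-risk and low-risk patients. The list of steps under Intervention puts the lifestyle assessment in the first screening step without calling it optional.

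**The concern.** The effect of PPA CMR is estimated by comparing the intervention group with the waiting-list group, so the endpoint variables should be collected in the same way in both. Here the baseline values of three of the six listed risk factors sit in a module that one arm may decline and the other meets as part of a single questionnaire.

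Two things are at stake. The first is selection. If those who skip the module differ in the behaviour being measured, the intervention patients with baseline data are a selected group and the controls are selected differently or not at all. Randomisation does not protect against this, because the loss comes after allocation and depends on the arm's procedure. The second is precision. Patients who take part but skip the module contribute less to the lifestyle endpoints, including smoking if it is asked only there. The sample size section allows for low response but does not mention responders without lifestyle data.

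**Working it through.** **1. The plan's own figure.** Inputs from Sample size calculation: smoking 20% v 25%, two-sided alpha 0.05, power 80%, ratio 1:4.

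- Pooled proportion = (0.20 + 4 × 0.25)/5 = 0.24.
- n = [1.960 × √(0.24 × 0.76 × 1.25) + 0.842 × √(0.16 + 0.1875/4)]² / 0.05² = (0.936 + 0.383)² / 0.0025 ≈ 696.
- With continuity correction: n/4 × [1 + √(1 + 2 × 1.25/(n × 0.05))]² ≈ 720.3, rounded up to **721**.

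The stated 721 is reproduced and is not in dispute. The matching control number is 4 × 721 = 2884.

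**2. The collection rules side by side.**

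| | PPA CMR invitees | Waiting-list controls |
|---|---|---|
| Risk estimation | asked | asked |
| Lifestyle assessment | optional | in the same questionnaire, no option stated |
| Paper form with reminder | risk estimation only | unclear (see below) |

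The optional wording conflicts with the Abstract and with Endpoints and measurements. Neither of those says how lifestyle is obtained from someone who declines the module. On paper forms, the Non-response analyses part of the Discussion sends them to all non-responders, so controls may get one too. Table 3 lists the paper risk estimation under non-response group 1, so it is unclear whether paper responders enter the endpoint comparison at all.

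**3. Which variables are affected.** Activity and diet are affected on any reading. Smoking is affected unless it is among the seven risk-estimation items; the printed list names about six and opens with a word that marks it as non-exhaustive. Body mass index and waist are in the risk estimation. Blood pressure, cholesterol and newly detected CMD come from the practice or its records. None of these depends on the lifestyle assessment.

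**4. Selection, for illustration.** The article gives no completion rates, so these are assumptions. Take true baseline smoking of 25% in both arms and controls fully observed. Let s and t be the shares of intervention smokers and non-smokers who complete the module:

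observed prevalence = 0.25s / (0.25s + 0.75t)

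- s = 0.70, t = 0.80: 0.175/(0.175 + 0.600) = **22.6%**, which is 2.4 points too low.
- s = 0.80, t = 0.70: 0.200/(0.200 + 0.525) = **27.6%**, which is 2.6 points too high.
- s = t: 25%, no distortion.

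These are shifts in observed baseline prevalence. How much reaches the estimated effect depends on how the analysis uses baseline.

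**5. Precision, for illustration.** This applies to smoking only if smoking is not in the risk estimation. Power = Φ[(0.05 − 1.960 × SE₀)/SE₁], with SE₀ from the pooled proportion, SE₁ from the separate proportions, no continuity correction and controls fixed at 2884.

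- 721 with data: SE₀ = 0.01778, SE₁ = 0.01694, power **81%**. It exceeds 80% because the 721 carries a continuity correction.
- 10% skip (649 with data): 78%.
- 30% skip (505 with data): SE₀ = 0.02068, SE₁ = 0.01955, power **69%**.
- 50% skip (about 360 with data): 55%.

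To keep 721 with data when 30% skip would take 721/0.70 = 1030 intervention patients.

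**The case against.** The strongest reply is that the optional wording may describe only how the programme is offered, while the research data are collected from everyone, as the Abstract and the endpoint section say. The article condenses a fuller protocol that may settle this. The control questionnaire is also not said to be compulsory, so controls could skip items too. This limits the point to what follows if the text is carried out as written. It does not remove the conflict, because the sentence that makes the module optional stands in the description of what intervention patients are actually asked to do.

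Smoking may well be an unprinted risk-estimation item. If so, the smoking and power illustrations fall away and only activity and diet remain, for which no figure can be given. That stands.

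Multiple imputation is planned. A reader might infer that it cannot help when data are missing by choice in one arm, but that goes too far. With arm in the model and with risk-estimation, record-based, linked socio-economic and later lifestyle data as predictors, it can be valid under missing at random. It may not correct fully if skipping depends on the behaviour itself, and willingness to change lifestyle, a natural predictor of skipping, is asked in the same module.

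The article reports no worried-well effect in the pilot. That concerns who took part, not which responders skip a module.

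Finally, the study aims to test the programme in routine care, where response is a known difficulty, so adding required items has a real if small cost.

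**Conclusion.** The point holds in a limited form and should be fixed. As written, baseline physical activity and diet, and smoking unless it is in the risk estimation, are optional in the intervention arm and bundled in the control arm. That conflicts with the statements that lifestyle is recorded for all participants. More frequent and selective missing baseline data in the intervention arm is a foreseeable risk of this wording, not an established fact.

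Its size and direction are unknown. The illustrations (22.6% or 27.6% observed against a true 25%; power from about 81% to 69% if 30% skip) rest on assumed completion rates and, for smoking, on its absence from the risk estimation.

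Stronger readings are not supported:

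- **That selection alone could produce the whole 5-point target effect.** This needs a chosen pair such as 60% v 80% completion (0.15/0.75 = 20.0%). The documents give no such rates, and the sign can reverse.
- **That the loss starts from about 87% power, using 40 × 21 = 840 intervention patients.** This treats the 15% added for clustering as free extra patients. Dividing by 1.15 gives about 730 and power of about 82%, close to the design.
- **That the paper form differs by arm.** The text leaves this open.

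The other components of endpoint 2, and newly detected CMD, are not touched.

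**What to change.** Reconcile the Abstract, Invitation of patients, Control group, and Endpoints and measurements on whether the lifestyle questions are required. The change itself is to make the same core smoking, physical activity and diet items a required part of the first questionnaire in both arms, before any risk score or advice is shown. Print those items on the paper form wherever paper responders enter the comparison, and say whether they do. The rest of the lifestyle assessment can stay optional. If smoking is already one of the seven risk-estimation items, say so; then only activity and diet need adding.

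The cost is a web-form setting, a few more printed questions, a slightly longer first questionnaire and possibly a small loss of response. The change has to be made before baseline, because baseline answers cannot be recovered afterwards.
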